### Intervention

The program is designed to be self-operating and is delivered through a secure web application created exclusively for this research (https://www.studioenforcer.it/EN).

It is designed to improve cognitive abilities, offer emotional and affective support, and aid in physical rehabilitation.

The one-year program will begin with six months of weekly educational sessions and interactive tasks, followed by six months of occasional reminders to exercise.

To effectively address the most affected areas, patients with cognitive impairment will begin with cognitive enhancement, those with emotional problems will begin with emotional support, and those with both will be randomly assigned to receiving emotional support first, followed by cognitive enhancement or vice versa.

After the initial presentation, all educational and interactive materials will be available for further practice. Physical rehabilitation education will be provided concurrently to ensure a gradual progression towards physical goals.

Caregivers of participants in the study will receive customized education via the web application. Concurrent medical, psychological, or physical therapies are permitted and will be observed at all follow-up stages of the study.

#### Cognitive functions enhancement (3 months)

Cognitive function enhancement educational materials will focus on information about the most common cognitive sequelae after cardiac arrest relative to attention, memory and executive functions, together with suggestions for their management.

Interactive exercises focus on attention (visual item search, go-no go, dual tasks and task switching exercises), memory (learning with immediate and deferred recall of lists of words and texts, immediate learning of visual matrices), executive functions (inhibitory control tasks, logic sequences and problem solving) and working memory (n°-back task, reordering of words lists and mental calculus).

Interactive exercises are graded into three different levels of difficulty, higher levels can be reached only after the correct completion of lower levels, and variability is granted by their continuous modification through artificial intelligence algorithms, to maximize the benefits and possibly increase adherence by avoiding the repetition of the same exercises.

#### Emotional support (3 months)

Emotional support educational material focuses on information about possible emotional-affective sequelae after cardiac arrest and their potential impact on social and personal life, along with strategies for coping. Suggested exercises focus on relaxation, breathing, mindfulness, sleep hygiene, and socialization.

#### Physical rehabilitation (6 months)

Physical rehabilitation materials address the importance of physical activity and proper nutrition in promoting physical and cognitive-emotional improvement. Practical exercises will be presented through pre-registered videos and vignettes.

Rehabilitation will begin with daily strengthening exercises for trunk and arm control and then will focus on aerobic activity, with the aim of achieving at least 150 min of moderate activity and at least 2 muscle-strengthening activities involving all major muscle groups,^27^ within 6 months of enrolment, and maintained for the last 6 months.

Participants will be advised to stop or reduce the intensity of exercises if they feel tired and, to adhere strictly to any physical activity restrictions required by their underlying condition or prescribed by their physicians.

#### Caregiver information

During the first three months, the caregivers in the intervention dyads will receive information about the affective and cognitive problems their relative is likely to experience after a cardiac arrest and about the strategies available to help them.

### Control group

Patients randomized to the control group will be followed up by their primary care physician (usual care). They will be asked to complete the diaries and all the assessments at the same scheduled follow-up visits and as the intervention group.

Throughout the study, participants will be allowed to receive concurrent pharmacological, psychological, or physical treatments. The concurrent use of medications such as antidepressants, anxiolytics, antipsychotics, opiates, and other analgesics, as well as any form of psychotherapy or physiotherapy, will be carefully recorded at the scheduled visits.

### Sample size

The sample size was defined assuming a 25 % difference in the primary outcome (the proportion of patients free of emotional or cognitive disorders at 12 months after enrolment, i.e. HADS<8 and/or TICS>31), i.e. 55 % in the intervention group vs. 30 % in the control group. A total sample size of 96 patients (48 per group) was estimated to be required to reject the null hypothesis of equal proportions in the two groups with 80 % power, an alpha error of 0.05, and a 1:1 randomization. Considering a dropout rate of 30 %, the final sample size was set at 137.

Based on the historical data of the participating centres, an annual flow of 350 patients is expected. According to literature reports that the prevalence of anxiety and depression symptoms is approximately 30 % of OHCA survivors^28^ and cognitive impairment is up to 50 %,^2^ we estimate that about 60–70 % (210–245 patients/year) of patients will be eligible for enrolment, therefore, the full sample size should be reached within 12 months from the beginning of the study. In case of slow recruitment, an extension of the enrolment period up to 24 months will be requested.

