### Data collection and statistical analysis plan

Questionnaires and diaries completed by participants will be collected directly via an electronic case report form (eCRF) integrated into a web application. The same application will facilitate data entry for the researcher conducting the observer-rated assessments, using a distinct user interface with unique login credentials. To ensure data quality, the rater will be trained in clinical assessment and completion of the observer-rated questionnaires. Participants will be automatically checked for data completeness, and they will receive regular reminders to ensure timely data entry.

The proportions of patients without cognitive or emotional symptoms 12 months after enrolment will be compared between groups using the z-test. A modified intent-to-treat approach will be used, including in the analysis patients who received at least one the web-based treatment session or standard care. To manage missing/incomplete data and to address a possible selection bias related to the modified intent-to-treat approach we will focus on the possible distribution of the missing data given the observed data. In order to do so, we will determine whether the distribution of patients’ unseen observations at the final visit, given their observations at previous visits and baseline, is different from that seen among the patients who have no missing data. To estimate the intervention effect at the end of the trial, we will make assumptions about how the patterns differ in the two groups of patients. We will then estimate the intervention effect amongst those who do, and do not have, missing data, which has to be averaged, to arrive at the overall estimate of the effect of intervention.^29^

Secondary outcome measures will be compared between the two groups using the *t*-test or Mann-Whitney *U* test according to their frequency distribution.

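### The 96 patients (48 per group) give the stated 80% power only with an undeclared one-sided 5% test; two-sided at 5%, the power is about 70%

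*Protocol article*

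**What the plan says.** The Sample size section of the protocol article gives all the inputs but one. The effect is "55 % in the intervention group vs. 30 % in the control group", and the calculation is made "with 80 % power, an alpha error of 0.05, and a 1:1 randomization". The result is: "A total sample size of 96 patients (48 per group) was estimated to be required to reject the null hypothesis of equal proportions". The allowance for loss follows: "Considering a dropout rate of 30 %, the final sample size was set at 137".

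Under Data collection and statistical analysis plan, the proportions without symptoms "will be compared between groups using the z-test".

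The missing input is the side of the test. The article uses neither one-sided nor two-sided anywhere. The null hypothesis is one of equal proportions, and the abstract and the Aims section describe the primary outcome as a difference between the groups, with no direction given.

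**The concern.** An unqualified alpha of 0.05 against a null hypothesis of equality is conventionally read as two-sided. On that reading 48 per group looks too small to detect 55% versus 30% with 80% power.

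Two things are at stake:

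- **If the final test is two-sided at 5%,** the printed power is too high, and a real 25-point effect is more likely to be missed than readers, funder and ethics committee were told.
- **If the final test is one-sided at 5%,** the chance of a false positive in favour of the intervention is 5%, against 2.5% in that direction for a two-sided 5% test. Readers would not know it.

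While the side stays open, a result with a two-sided P value between 0.05 and 0.10 in favour of the intervention could be called positive or negative after the event.

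**Working it through.** **Inputs, all from the Sample size section.** p1 = 0.55, p2 = 0.30, difference 0.25, power 80% (z = 0.8416), alpha 0.05, 1:1 allocation. The mean proportion is (0.55 + 0.30)/2 = 0.425. The analysis section names the z-test and mentions no continuity correction.

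**Formula (pooled variance under the null hypothesis), per group:**

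n = [z_a × sqrt(2 × 0.425 × 0.575) + 0.8416 × sqrt(0.55 × 0.45 + 0.30 × 0.70)]² / 0.25²

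The two square roots are sqrt(0.48875) = 0.6991 and sqrt(0.4575) = 0.6764.

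**Step 1. Reproduce the plan's figure.** With one-sided 5%, z_a = 1.645:

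n = [1.645 × 0.6991 + 0.8416 × 0.6764]² / 0.0625 = 47.29, so 48 per group and 96 in total. This matches the protocol exactly.

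**Step 2. The same formula, two-sided 5%,** z_a = 1.960:

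n = [1.960 × 0.6991 + 0.8416 × 0.6764]² / 0.0625 = 60.19, so 61 per group and 122 in total.

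**Step 3. Does another standard formula give 96 two-sided?** Total sample sizes for 80% power:

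| Formula | One-sided 5% | Two-sided 5% |
|---|---|---|
| Pooled z-test | 96 | 122 |
| Arcsine | 96 | 120 |
| Unpooled z-test | 92 | 116 |
| Continuity-corrected | 110 | 136 |

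No two-sided version gives 96. Without continuity correction the gap is 20 to 26 patients, too large to be rounding.

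**Step 4. Power with 48 per group.** Power = Φ([0.25 × sqrt(48) − z_a × 0.6991] / 0.6764):

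- Two-sided: Φ((1.7321 − 1.3702)/0.6764) = Φ(0.535) = 70.4%.
- One-sided: Φ((1.7321 − 1.1499)/0.6764) = Φ(0.861) = 80.5%.

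Exact binomial enumeration of the pooled z-test gives 70.8% two-sided and 81.5% one-sided. The arcsine and unpooled approximations give 70.8% and 72.6% two-sided. A continuity-corrected z-test or Fisher's exact test, neither of which is planned, would have 63.0%.

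**Step 5. Detectable difference.** With 48 per group, two-sided, 58% versus 30% has 79.9% power. The difference detectable with 80% power is therefore about 28 points, not 25.

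**Step 6. Does the dropout allowance cover the gap?** 96/0.70 = 137.1, so the 137 allows only for the assumed 30% loss and returns to about 96 evaluable patients. Two-sided 80% power needs 122 evaluable; 122/137 = 0.89, so dropout could be no more than about 11%. With dropout kept at 30%, 122/0.70 = 174.3, so 175 would have to be randomised.

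**The case against.** The strongest reply is that the document contradicts nothing it states. It never says two-sided, and read as a one-sided 5% design its figures agree exactly. A null of equal proportions is sometimes written loosely for a one-sided superiority test, and the side may be given in a full protocol or analysis plan that is not shown. On this view the fault is an undeclared side, not a wrong calculation.

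Part of this stands. The power shortfall is conditional: it exists only if the final z-test is two-sided. If the test really is one-sided at 5%, the 80% is right, and what remains is to declare and justify that choice. But an unseen document can only settle the side. It cannot make 96 evaluable patients give 80% power two-sided. The article prints a sample size, a power and an alpha that fit together only under an assumption that is neither stated nor the default.

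A second reply is that 30% dropout is a planning assumption, and that the modified intention-to-treat analysis also estimates the effect in patients with missing outcomes, so real power need not equal that of 96 completers. That is fair: two-sided power would be about 74% with 52 evaluable per group, 76% with 55 and 80.5% with 61. But patients without a 12-month outcome add little information, so this does not restore 80% at the dropout the plan assumes.

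Finally, a two-sided 5% test on 96 patients keeps its type I error and the estimate is valid; the cost is lost power and a misleading power statement. That limits the harm, but the statement concerns the main design figure for the primary outcome.

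**Conclusion.** The concern holds. The figure of 96 is reproduced only by a one-sided 5% calculation, which the protocol article does not declare. Under the conventional two-sided 5% reading, the power at the planned 96 evaluable patients is about 70% (70 to 73% across formulas without continuity correction), not 80%. The chance of missing a true 25-point effect is about 30% rather than 20%, and the shortfall is 26 evaluable patients by the pooled formula.

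This rests on the protocol's own 55% and 30%, equal groups, the uncorrected z-test and the assumed 30% dropout. Only the two-sided reading is brought in from convention. If one-sided 5% was meant, the power statement is correct, but the level must be declared, because it allows twice the false-positive rate in favour of the intervention that a two-sided 5% test allows.

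**What to change.** Declare the side of the test before the data are analysed, in the same terms in the Sample size section and for the primary z-test.

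- **If two-sided 5%,** replace the power statement with, for example:

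> With a two-sided 5% z-test, 96 evaluable patients give about 70% power for 55% versus 30%, and 80% power for about 58% versus 30%.

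- **If one-sided 5%,** say so in both places, give the reason, and report the result as a one-sided test.

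Either correction is one sentence and needs no extra patients; in the two-sided case the stated power becomes less favourable. Keeping 80% power for 55% versus 30% with a two-sided test is a separate and costlier choice: about 122 evaluable patients, or about 175 randomised at 30% dropout, which is 38 more than the planned 137. The section already foresees extending enrolment to 24 months, but only for slow recruitment, so using that period for a larger target would need its own justification and amendment.

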### Data collection and statistical analysis plan

Questionnaires and diaries completed by participants will be collected directly via an electronic case report form (eCRF) integrated into a web application. The same application will facilitate data entry for the researcher conducting the observer-rated assessments, using a distinct user interface with unique login credentials. To ensure data quality, the rater will be trained in clinical assessment and completion of the observer-rated questionnaires. Participants will be automatically checked for data completeness, and they will receive regular reminders to ensure timely data entry.

The proportions of patients without cognitive or emotional symptoms 12 months after enrolment will be compared between groups using the z-test. A modified intent-to-treat approach will be used, including in the analysis patients who received at least one the web-based treatment session or standard care. To manage missing/incomplete data and to address a possible selection bias related to the modified intent-to-treat approach we will focus on the possible distribution of the missing data given the observed data. In order to do so, we will determine whether the distribution of patients’ unseen observations at the final visit, given their observations at previous visits and baseline, is different from that seen among the patients who have no missing data. To estimate the intervention effect at the end of the trial, we will make assumptions about how the patterns differ in the two groups of patients. We will then estimate the intervention effect amongst those who do, and do not have, missing data, which has to be averaged, to arrive at the overall estimate of the effect of intervention.^29^

Secondary outcome measures will be compared between the two groups using the *t*-test or Mann-Whitney *U* test according to their frequency distribution.

Factors associated with emotional and/or cognitive dysfunction will be identified using logistic regression models. The dependent variable will be the presence or absence of clinically relevant depression/anxiety (HADS≥8) and/or cognitive impairment (TICS≤31) and independent variables will include patient-related and hospital-related variables. All the patients screened for potential participation in the ENFORCER trial will be included in this analysis. Due to the elevated number of candidate variables to test, the model will be trained in 70 % of the sample using a LASSO (least absolute shrinkage and selection operator) regularization technique to prevent overfitting^30^ and tested in the remaining 30 % of the sample.

Finally, the validation of the Italian version of the SISS will be performed through translation and back-translation of the original version to ensure the semantic equivalence between the two versions. The internal validity of the scale will be assessed by examining the structure and internal consistency of the scale using exploratory factor analysis and Cronbach’s alpha coefficient. The concurrent validity of the SISS with SF-12 and HADS will be investigated using Spearman’s correlation coefficient.

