### Aims

The primary aim is to evaluate the effectiveness of internet-based lifestyle interventions on anxiety, depression and cognitive impairment in OHCA survivors with good neurological recovery compared to usual care. The primary outcome is the difference in the proportion of patients without cognitive or emotional symptoms between the two groups one year after enrolment.

The first secondary aim is to evaluate the effectiveness of internet-based lifestyle interventions on HRQoL, behavioural efficiency, and sleep quality in OHCA survivors with good neurological recovery. Outcomes will be assessed at baseline and at 1-, 3-, 6-, and 12-months post-randomization with continuous log-data collection for user engagement.

Other secondary aims include the assessment of caregivers’ HRQoL, anxiety and depression, sleep quality and burden, the validation of the Italian version of the Sexual Interest and Satisfaction Scale (SISS) and the identification of factors associated with anxiety and depression in OHCA survivors with good neurological recovery.

Primary and secondary objectives and outcome measures are listed in Table 1.

**Table 1 t0005:** Outcomes and Outcome Measures of the ENFORCER study.

Outcome	Outcome measure
Primary endpoint	
Effectiveness of internet-based lifestyle interventions on anxiety, depression and cognitive impairment	Proportion of patients without cognitive or emotional symptoms (HADS<8 and TICS>31) one year after enrolment
Secondary endpoints	
Effectiveness of internet-based lifestyle interventions on patients’ health-related quality of life, sleep quality, behavioral efficiency, sexual function, and on caregivers’ burden, health-related quality of life, sleep quality and emotional symptoms	Short Form Health Survey 12 (SF-12) Pittsburgh Sleep Quality Index (PSQI) Neurobehavioral rating scale (NRS) Patient Competency Rating Scale (PCRS) Sexual Interest and Satisfaction Scale (SISS) Zarit Burden Inventory (ZBI)
Factors associated with emotional or cognitive impairment	Presence or absence of the cognitive or emotional symptoms at enrollment (t_-1_)
Italian validation of the Sexual Interest and Satisfaction Scale	−

Abbreviations: HADS – hospital anxiety and depression scale; TICS – telephone interview for cognitive status.

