### Study design and setting

ENFORCER is an interventional parallel-group randomized controlled trial. Recruited participants will be randomized 1:1 to the intervention or control group using simple computerized randomization obtained at the time of enrolment.

The 38 collaborating institutions will refer potentially eligible patients to the coordinating centre for participation, but also caregivers and self-referral are allowed.

All outpatients who meet the eligibility criteria will be recruited after discharge from hospital, regardless of geographic location.

A trained neuropsychologist, blinded to patient group allocation, will conduct the clinical assessments. All professionals involved in data management and analysis will also be blinded to group allocation. Unblinding will be possible only at the request of the Data Safety and Monitoring Board (DSMB).

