### Eligibility criteria

OHCA survivors within 15 days of hospital discharge will be considered eligible for randomization. Inclusion criteria will be age 18–80, no history of severe mental or neurological illness, a good neurological outcome (CPC 1–2) at hospital discharge, Hospital Anxiety and Depression Scale – HADS^18^ score ≥ 8 and/or cognitive impairment (Telephone Interview for Cognitive Status^19^ – TICS score ≤ 31.

Italian language skills and Internet literacy will be required to ensure compliance with treatment and interviews. Prior to enrolment, patients will be asked to give their consent to participate in the study and to have their personal data processed, after an explanation of the study objectives and procedures and an opportunity to ask questions.

Survivors experiencing anxiety, depression, or cognitive impairment will be randomly assigned to the intervention or the control group. For each survivor recruited, a caregiver will also be included in the study, and given access to a parallel account on the web application.

Individuals who do not meet the criteria for anxiety, depression, or cognitive impairment will not be included in the trial and allocated to the treatment groups. However, baseline information will be collected for the secondary analysis to identify factors associated with these conditions after hospital discharge.

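### The unadjusted primary z-test is valid but leaves baseline HADS and TICS out of the effect estimate, giving up precision that needs no new data

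*Protocol article*

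**What the plan says.** All references are to the protocol article.

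- **Primary test** (Data collection and statistical analysis plan): "The proportions of patients without cognitive or emotional symptoms 12 months after enrolment will be compared between groups using the z-test". No covariate is named.
- **Allocation** (Study design and setting): 1:1, "using simple computerized randomization obtained at the time of enrolment". No stratification or minimisation is described.
- **Endpoint** (Aims, Table 1): "Proportion of patients without cognitive or emotional symptoms (HADS<8 and TICS>31) one year after enrolment".
- **Entry** (Eligibility criteria): a HADS "score ≥ 8 and/or cognitive impairment" on TICS, with the complementary cut-offs (HADS 8 or more, TICS 31 or less). The Intervention section orders the modules by whether a patient has the emotional deficit, the cognitive deficit or both, so both scores must be known at the start.
- **Other use of baseline** (Data collection and statistical analysis plan): unseen final-visit values are considered "given their observations at previous visits and baseline", and the effects in patients with and without missing data are then averaged.
- **Planning values** (Sample size): "55 % in the intervention group vs. 30 % in the control group", 80% power, alpha 0.05 with sidedness not stated, 48 per group, and 137 in total after 30% dropout.

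**The concern.** Success at 12 months means being on the right side of two cut-offs. Every randomised patient starts on the wrong side of at least one, by an amount already recorded. A patient with both deficits has to cross two thresholds; a patient with one has to cross one and hold the other. It is plausible that baseline scores carry information about success, yet neither the allocation nor the primary test uses it.

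Two things are at stake. One is precision, in a trial planned on 96 evaluable patients. The other is the reading of the result if the arms happen to differ in severity, because the unadjusted difference in proportions has no means of correcting for that.

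**Working it through.** **1. Reproduce the plan's figure.** Inputs from Sample size: p1 = 0.55, p0 = 0.30, power 0.80, alpha 0.05. Mean proportion 0.425.

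n per arm = [z_α √(2 × 0.425 × 0.575) + z_β √(0.55 × 0.45 + 0.30 × 0.70)]² / 0.25²

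- One-sided: (1.645 × 0.6991 + 0.8416 × 0.6764)² / 0.0625 = 47.3, so 48 per arm. This matches the stated 96.
- Two-sided: (1.960 × 0.6991 + 0.8416 × 0.6764)² / 0.0625 = 60.2, so 61 per arm (122).
- Dropout: 96 / 0.7 = 137.1, against the stated 137.

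Power of a two-sided z-test at 48 per arm: null SE √(0.48875/48) = 0.1009; alternative SE √(0.4575/48) = 0.0976; (0.25 − 1.96 × 0.1009)/0.0976 = 0.535, which gives 70.4%. One-sided it is 80.5%.

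**2. How often severity is imbalanced.** Under simple 1:1 randomisation the standardised difference in a baseline score has SD of about 2/√N.

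- N = 96: SD 0.204; P(difference above 0.25 SD in either direction) = 0.22.
- N = 137: SD 0.171; the same probability is 0.14.

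**3. What adjustment gains.** The article gives no prognostic strength for the baseline scores, so a range of control-arm AUCs is assumed. Simulated trials (6,000 per setting) used simple randomisation, 55% vs 30% success and two continuous baseline covariates. The pooled z-test was compared with a logistic model on arm and both covariates (likelihood-ratio test; standardised risk difference). Results at N = 96:

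| Assumed AUC | Two-sided power, z-test → adjusted | One-sided power, z-test → adjusted | Variance ratio of risk difference | N for 80% two-sided (122 × ratio) |
|---|---|---|---|---|
| 0.66 | 0.71 → 0.74 | 0.81 → 0.83 | 0.950 | 116 |
| 0.74 | 0.71 → 0.78 | 0.80 → 0.87 | 0.848 | 104 |
| 0.81 | 0.70 → 0.83 | 0.80 → 0.90 | 0.756 | 93 |

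Repeat runs gave adjusted two-sided power of 0.72 at AUC 0.63, 0.74–0.75 at 0.67, up to 0.80 at 0.74 and up to 0.84 at about 0.80. The mean risk difference stayed near 0.25 under both methods, so the target quantity is unchanged.

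With uninformative covariates (AUC 0.50), power was 0.704 for the z-test and 0.708 adjusted, with a variance ratio of 1.02.

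**4. Type I error.** With no effect (30% in both arms, AUC 0.74, N = 96), the z-test rejected in 4.7% of trials and the adjusted test in 5.3%. Across the AUC settings the adjusted test ran from 5.0% to 5.7%, so a small part of its power gain comes from being slightly liberal. The variance ratios do not depend on this.

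Among the null trials with imbalance above 0.25 SD, the z-test rejected in 8.6% and the adjusted test in 5.3%. When the imbalance favoured the intervention arm, the unadjusted difference was shifted by 6.6 points on average and the adjusted one by 0.4.

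**The case against.** The strongest reply is that nothing in the plan is wrong. The z-test is valid under simple randomisation, its overall type I error is nominal, and it matches the hypothesis used for the sample size ("to reject the null hypothesis of equal proportions in the two groups with 80 % power"). The shift in imbalanced trials is conditional variation that the unconditional standard error already covers. All of this stands: the point is about efficiency and robustness of interpretation.

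Several stronger readings are tempting, and the article does not support them:

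- **The z-test is biased or invalid.** It is neither.
- **Baseline is ignored altogether.** It enters the missing-data step and so, with 30% dropout planned, part of the averaged estimate. It is absent from the named comparison.
- **Baseline severity strongly predicts success.** No section says so. Truncation of the scores at the eligibility cut-offs may weaken the prediction; the mix of deficit types may strengthen it.
- **Imbalance in deficit type alone does large damage.** Take the Sample size prevalences of 30% and 50% as independent: 0.15/0.65 = 23% of eligible patients have both deficits. At 137 patients that share differs by 10 points or more in 16% of randomisations. If such patients succeed at 15% and the others at 34.5% (about 30% overall), a 10-point imbalance shifts the estimate by 0.10 × 19.5 = about 2 points. If they never succeed, the shift is 0.10 × 39 = 3.9 points. The standard error is 9.8 points.
- **Adjustment repairs the sample size.** The 70% two-sided power comes from an unstated sidedness, which is a separate matter. At the lower AUCs adjustment does not reach 80%.
- **Unequal arm sizes justify the change.** Simple randomisation allows them, but adjusting for HADS and TICS does not correct them.

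An unseen statistical analysis plan might add an adjusted analysis as supportive. The article nevertheless fixes the unadjusted test as primary.

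**Conclusion.** The point holds as a worthwhile improvement to a valid analysis. The primary estimate leaves out two baseline scores that are known for every randomised patient and share their cut-offs with the endpoint.

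In round terms, at 96 evaluable patients and two-sided 0.05, power goes from about 70% to 72–75%, 78–80% or 83–84% as the assumed AUC goes from 0.63–0.67 to about 0.74 to about 0.80. The variance of the risk difference falls by about 5–25%. The direction is secure, because the cost is negligible if the scores carry no information. The size is not, because it rests wholly on assumed prognostic strength and on simulated covariates not truncated at the entry cut-offs.

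**What to change.** Before unblinding, prespecify as the primary analysis a logistic model for 12-month success on arm, baseline HADS and baseline TICS, both continuous. Standardise it over all analysed patients to give an adjusted risk difference with a robust two-sided 95% CI. Use the same model within the planned averaging over patients with and without missing data, so that one estimate results. Keep the unadjusted z-test as a supportive analysis.

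No new data are needed, and a change to stratified randomisation is not part of this. The Study design and setting section keeps those who manage and analyse data blinded to allocation, so the model can still be fixed credibly although recruitment began in August 2024. The cost is a protocol amendment with Ethics Committee approval, documented on the registry as the Trial status section requires, and slightly more analysis work.
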